#### Mindfulness

The Five Facet Mindfulness Questionnaire- Short Form (FFMQ-SF) [75] will be used to measure mindfulness, defined as the ability to bring one’s attention to experiences in the present moment in a non-judgmental way [76]. The questionnaire contains 24 items that measure five facets of mindfulness: observing; describing; acting with awareness; non-judging; and non-reactivity. Items are scored on a 5-point scale ranging from 1 (never or very rarely true) to 5 (very often or always true). A psychometric study showed that the FFMQ-SF is a sensitive, reliable, and valid instrument. Furthermore, the five-factor structure of the questionnaire was confirmed in this study [75].

#### Generic health status and quality of life

The EuroQol-5 Dimensions-5 Levels questionnaire (EQ-5D-5 L) measures general quality of life using five dimensions (i.e. mobility, self-care, usual activities, pain/discomfort, and anxiety/depression) [77]. Each dimension has five response categories, describing the severity of problems. A total of 3125 unique health states can be defined, by combining the responses for the five dimensions into a five-digit number (ranging from “11111” meaning no problems at all to “55555” meaning extreme problems in all five dimensions) [78]. The EQ-5D-5 L is an adaption of the EQ-5D [79]. The EQ-5D consists of the same five dimensions but has only three response categories per dimension. Evidence suggests that the EQ-5D has limited responsiveness to changes in health, partly caused by ceiling and floor effects. Studies show that compared to the EQ-5D, the EQ-5D-5 L has smaller ceiling and floor effects, and improved reliability and discriminating ability [80, 81].

#### Costs associated with psychiatric illness

For calculating the total direct medical costs, the Trimbos/iMTA questionnaire for Costs associated with Psychiatric Illness (TiC-P) [82] will be used. The TiC-P measures utilization of medical treatment, such as the number of contacts with the general practitioner and multiple other care providers (e.g. medical specialists and paramedics) during the last four weeks, as well as medication use and loss of productivity at (voluntary) work. The costs will be calculated using the Dutch guidelines for cost calculations in healthcare. Reference unit prices of the corresponding healthcare services will be applied. A psychometric study demonstrated that the Dutch version of the TIC-P is a feasible, reliable, and valid tool for assessing care consumption and productivity loss in patients with mild to moderate psychiatric problems [83].

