Each participant will complete four main measurements during the study: before the start of the intervention (and before participants are informed about which intervention they will receive) (T0); directly following the intervention (three months after baseline; T1); and six (T2) and twelve months (T3) after baseline. All measurements consist mainly of online self-report questionnaires. T0, T1, and T3 also include a telephone interview conducted by a research assistant. The research assistant that conducts the telephone interviews will be unaware of treatment allocation of the participants. If for any reason this blinding is broken, another research assistant (that is blind to treatment condition of the participant) will take over the telephonic assessment.

Figure 1 shows the flow chart of the study design. The SPIRIT Checklist and Figure are presented as Additional file 1 and 2 respectively. The study is approved by the medical ethical committee of the Leiden University Medical Center (LUMC; no. P16.248).

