
#### Procedure during study participation

During the intervention, participants will fill in a short questionnaire assessing potential mediator variables several times. At these moments they will also complete the GAD-2 [55] and PHQ-2 [56] to measure respectively anxiety and depression symptoms (the combination of PHQ-2 and GAD-2 is also known as the PHQ-4 [57]). They will also be asked whether they have had recurrent thoughts about death or hurting themselves in the past week, using an item of the PHQ-9 [49]. When participants have had suicidal thoughts in the past week, they will be recommended to discuss this with their mental health counselor at the general practice. Furthermore, their mental health counselor will be notified about the presence of suicidal thoughts by the researchers and are asked to contact the participant. Participants in the experimental condition complete this questionnaire at the end of every online lesson (nine times in total). Participants in the control condition, receive an email with a link to this questionnaire after every session with the mental health counselor (a total of four times).

Both interventions are delivered in a timespan of maximum 12 weeks, after which participants receive an e-mail with a link to the online self-report questionnaires of the post-treatment assessment (T1). T1 also includes a clinical interview by telephone conducted by a research assistant. The follow-up assessments take place six (T2) and twelve months (T3) after baseline. Both these assessments consist of self-report questionnaires and T3 also includes a clinical telephone interview. Figure 1 shows an overview of the patient flow through the phases of the study.

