### Assessments

Table 1 depicts an overview of the assessment instruments that will be used throughout the study. All questionnaires—except for the M.I.N.I.-Plus and SDS—will be conducted online. The M.I.N.I.-Plus and SDS are conducted by telephone.

**Table 1 Tab1:** Overview of assessments during the study

Assessment	Screening	T0 Baseline	During intervention	T1 Post-intervention (14 weeks after T0)	T2 Follow-up (26 weeks after T0)	T3 Follow-up (52 weeks after T0)
GAD-7	X	X	–	X	X	X
PHQ-9	X	X	–	X	X	X
PHQ-4 (GAD-2 + PHQ-2)	–	–	X	–	–	
M.I.N.I.-Plus	X	–	–	X	–	X
SDS	X	–	–	X	–	X
CERQ	–	X	–	X	X	X
AAQ-II	–	X	–	X	X	X
MHC-SF	–	X	–	X	X	X
FFMQ-SF	–	X	–	X	X	X
EQ-5D-5 L	–	X	–	X	X	X
TIC-P	–	X	–	–	X	X
CSQ-8	–	–	–	X	–	–
Self-esteem,Mastery andSupport	–	X	–	–	–	–
Life events	–	X	–	–	–	–
Somatic problems	–	X	–	–	–	–
Demographics and other information	–	X	–	–	–	–
Treatment credibility and expectancy	–	–	X	–	–	–
Emotion regulation	–	X	X	X	X	X
Behavioral avoidance	–	X	X	X	X	X
Treatment expectancy	–	–	X	–	–	–
Self-efficacy	–	–	X	–	–	–
SRS	–	–	X	–	–	–

*GAD-7* General Anxiety Disorder 7, *PHQ-9* Patient Health Questionnaire 9, *PHQ-4* Patient Health Questionnaire 4,*GAD-2* General Anxiety Disorder 2, *PHQ-2* Patient Health Questionnaire 2, *M.I.N.I.-PLUS*, Mini-International Neuropsychiatric Interview-PLUS, *SDS* Sheehan Disability Scale, *CERQ* Cognitive Emotion Regulation Questionnaire, *AAQ-II* Acceptance and Action Questionnaire II, *MHC-SF* Mental Health Continuum Short Form, *FFMQ-SF* Five Facet Mindfulness Questionnaire Short Form, *EQ-5D-5 L* EuroQol 5 dimensions 5 levels questionnaire, *TiC-P* Trimbos/iMTA questionnaire for Costs associated with Psychiatric Illness, *CSQ-8* Client Satisfaction Questionnaire 8, *SRS* Session Rating Scale

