To examine moderators of the treatment outcome, longitudinal multi-level regression analysis will be performed. Potential moderators will be entered individually in the model. Interaction effects will be investigated (e.g. time × condition × potential moderator). Bivariate latent difference score models will be used for the mediation analysis. This type of analysis is recommended for repeated measurements and multiple mediators, because they allow for a more dynamic approach to mediation, by assessing changes in multiple variables and their interrelations over time [103–105]. Cost-effectiveness analyses will be conducted in agreement with the CHEERS statement [106] and will be determined by relating the difference in healthcare costs (measured with the TiC-P) to the between-group difference in reliable change on GAD-7 scores (cost-effectiveness analysis) and quality-adjusted life-years (QALYs) gained based on the EQ-5D-5 L using the Dutch tariffs (cost–utility analysis). Productivity losses in paid work will be included in the economic evaluation and measured by assessing work-loss days due to absenteeism and work cutback days (presenteeism) while at work but not feeling well. All cost prices will be indexed for the appropriate reference year (likely to be 2017) but not discounted because the study’s time horizon does not exceed the period of a single year. Stochastic uncertainty in the incremental cost-effectiveness ratios (ICERs) will be handled using non-parametric bootstraps (2500 replications), plotted on the ICER plane and depicted in an ICER acceptability curve. Sensitivity analyses will focus on the friction cost versus human capital method and on main cost-drivers.

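### With a four-week recall for care contacts and no administration at T1, the TiC-P directly observes 8 of 52 follow-up weeks and none of the treatment period

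*Protocol article*

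**What the plan says.** The section Costs associated with psychiatric illness assigns the TiC-P the task of measuring direct medical costs. It counts contacts with the general practitioner and "multiple other care providers (e.g. medical specialists and paramedics) during the last four weeks". The same sentence continues "as well as medication use and loss of productivity at (voluntary) work", with no separate recall period for those items.

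Table 1 ("Overview of assessments during the study") marks the TiC-P at T0, at "T2 Follow-up (26 weeks after T0") and at T3, 52 weeks after T0. The cells for the intervention period and for T1 (14 weeks after T0) carry a dash. In the same table the EQ-5D-5L is marked at T0, T1, T2 and T3.

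On the timing of treatment, the Design section places the first measurement "before the start of the intervention (and before participants are informed about which intervention they will receive) (T0"). The section Procedure during study participation says "Both interventions are delivered in a timespan of maximum 12 weeks".

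The Statistical analysis section bases the economic evaluation on "relating the difference in healthcare costs (measured with the TiC-P"), which it sets against reliable change on the GAD-7 and against QALYs from the EQ-5D-5L. Costs are "not discounted because the study’s time horizon does not exceed the period of a single year". No other source of healthcare costs is named.

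**The concern.** Cost-effectiveness is part of the stated aim, and the Discussion counts the twelve-month comparison among the study's strengths. The cost side of that comparison rests on one instrument with a short look-back, given at two widely spaced points after baseline. Neither look-back reaches into treatment.

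If one intervention changes how often participants see the general practitioner, specialists or other providers, treatment is the most plausible time for it. No TiC-P window can see that change. The effect side does have a measurement at the end of treatment, because both the GAD-7 and the EQ-5D-5L are given at T1. Within one ICER, costs are therefore sampled more sparsely than effects, and the missing point is the one closest to treatment.

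The planned handling of uncertainty does not address this. The 2500 bootstrap replications reflect sampling variation in the data collected. The listed sensitivity analyses concern how productivity is valued and the main cost drivers. Neither brings in information on weeks that nobody was asked about.

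**Working it through.** The article states no coverage figure, so there is none to reproduce. The calculation uses only its recall period and its schedule.

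**Inputs**
- Recall for care contacts: 4 weeks (Costs associated with psychiatric illness).
- Administrations: weeks 0, 26 and 52 (Table 1).
- Horizon: 52 weeks (Statistical analysis; one year).
- Treatment: weeks 0 to 12 at most (Procedure during study participation); T1 at week 14 (Table 1).

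**Coverage as planned.** An administration at week t observes weeks t − 4 to t.
- T0: weeks −4 to 0, wholly before treatment.
- T2: weeks 22 to 26.
- T3: weeks 48 to 52.
- Follow-up observed: (4 + 4) / 52 = 8/52 = 15.4%. Not observed: 44/52 = 84.6%.
- Overlap with treatment: 0 of 12 weeks; up to T1, 0 of 14 weeks.
- The T2 window opens 22 − 12 = 10 weeks after the latest end of treatment, and 22 − 14 = 8 weeks after T1.

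**What filling the gap would rest on.** The article gives no filling rule, so take linear interpolation between window midpoints as an assumption. The T0 midpoint is week −2 and the T2 midpoint is week 24, which are 26 weeks apart. Let Δ be the arm difference in weekly contact cost at week 24, and assume no difference before treatment. The interpolated difference at week t is then Δ × (t + 2)/26. At week 6, mid-treatment, this is Δ × 8/26 = 0.31Δ. If the arms have converged by weeks 22-26, Δ = 0 and the interpolated treatment-phase difference is 0, whatever the true difference was. The treatment-phase estimate contains no treatment-phase data.

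**Coverage with T1 added**
- Four-week recall at week 14: weeks 10-14 are added, giving (4 + 4 + 4)/52 = 12/52 = 23.1%. This covers 2 of 12 treatment weeks and 4 of the 14 weeks up to T1. The Design section puts T1 at three months; at week 13 the total is still 12 of 52, with 3 of 12 treatment weeks.
- T1 form asking about the period since baseline, T2 and T3 unchanged: (14 + 4 + 4)/52 = 22/52 = 42.3%, with all 12 treatment weeks covered for the items asked.
- For comparison, a 13-week recall at T1, T2 and T3 covers 38/52 = 73.1%. Full coverage from T2 and T3 alone would need a 26-week recall.

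**The case against.** The case on the other side has real force, and several of its points limit what can be claimed.

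- *A reader might infer that 85% of the year is never costed.* The article does not support that. It shows only that those weeks fall outside a TiC-P window for contacts. It aims at total direct medical costs over one year and nowhere says that unobserved weeks count as zero. A filling rule is the kind of detail that a condensed article leaves to the analysis plan.
- *A reader might infer that the cost of delivering the interventions is missing from the ICER.* The article does not say so. Both arms have four planned counselor sessions, each followed by a counselor questionnaire, and both include training and supervision. Delivery can be costed bottom-up without a patient questionnaire. The planned difference between arms lies mainly in the web module and text messages.
- *A reader might infer that costs and effects cover different periods.* Both run from baseline to week 52, and QALYs too are interpolated between time points. What differs is how densely each is sampled.
- *A reader might infer that the ICER could have the wrong sign.* Nothing in the article allows that to be calculated. It gives no unit costs or expected contact rates.
- The 84.6% holds for care contacts only, since no recall is stated for medication or productivity loss.
- Longer recall trades coverage against recall error. Stretching it to 26 weeks would depart from the period the article describes for this instrument.

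What these points do not answer is that recall and schedule are data-collection decisions. An analysis plan can select a way to fill the treatment phase, but it cannot supply contacts that were never asked about.

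**Conclusion.** The point holds as a weakness in data collection for the economic evaluation. For care contacts, the only named source of the healthcare cost difference directly observes 8 of 52 follow-up weeks (15.4%) and none of the treatment period, whether that is counted to week 12 or to week 14. Treatment-phase contacts would have to be filled from one window before treatment and another that opens at week 22.

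This rests on reading the four-week recall as applying to contacts, on the Table 1 schedule, and on no further cost instrument being in use. That treatment is when the arms most plausibly differ in other care is a judgement; the article does not show it. The direction and size of any error in the ICER are unknown.

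The primary analysis of the GAD-7 at T1 and the sample size are untouched. The matter should be fixed, because cost-effectiveness is a stated aim and the remedy is cheap, but it does not threaten the trial's main clinical result.

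**What to change.** 1. Add the TiC-P to the online battery already given at T1. With the four-week recall unchanged, coverage of contacts rises from 8 to 12 of 52 weeks and the cost side gains data from weeks 10-14.
2. Optionally, let the T1 form ask about the main cost drivers since baseline, which would cover the whole treatment phase for those items. The recall at T2 and T3 can stay as it is.
3. State that delivery of both interventions is costed bottom-up, from the counselors' per-session records plus the web module. Exclude study sessions from the TiC-P contact count so that they are not counted twice.
4. State how weeks between windows are filled, and vary that rule in a sensitivity analysis.

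The cost is one more online questionnaire at an existing time point and a protocol amendment. Respondent burden rises slightly, and recall error grows if the T1 window is lengthened. Recruitment began in November 2017, so participants already past T1 when the change takes effect would have no T1 cost data and must be handled as missing at that point. The earlier the change is made, the fewer there will be.

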#### Client satisfaction

The Client Satisfaction Questionnaire-8 (CSQ-8) [81] is an eight-item instrument that is designed to measure client satisfaction with services. The items for the CSQ-8 were selected based on mental health professionals’ ratings of a number of items that could be related to client satisfaction and a subsequent factor analysis. The CSQ-8 is uni-dimensional, yielding a homogeneous estimate of general satisfaction with services. The questions are answered on a 4-point scale in the range of 1–4, but each question has different labels attached to these values. Higher scores indicate higher client satisfaction. The psychometric qualities of the Dutch translation of the CSQ are adequate [84, 85].

### Moderator variables

#### Self-esteem, mastery, and support

Starting from existing instruments, Bovier, Chamot, and Perneger used factor analyses to develop four brief scales for the assessment of self-esteem, affective social and confident/problem-solving social support [86]. All 12 items are answered on a 5-point Likert scale, with higher scores representing higher levels of the four measured constructs. All four scales have been found to demonstrate good internal and construct validity [86].

#### Life events

A self-developed questionnaire will be used to measure negative life events and associated distress. Participants are asked if they have experienced negative life events in the past six months and/or earlier in their life. If they indicate that they have experienced such (an) event(s), they are asked to rate them on an 11-point scale (ranging from 0 [not at all] to 10 [extremely]) to what extent these experiences currently still evoke strong negative feelings.

#### Co-morbid somatic problems

Co-morbid physical problems will be measured with a self-developed questionnaire listing 25 (chronic) conditions. This list is based on information from Statistics Netherlands. Participants will also be asked to rate to what extent their somatic problem(s) interferes with their current daily functioning on an 11-point scale ranging from 0 (not at all) to 10 (extremely).

#### Socio-demographics and other information

Using a self-developed questionnaire, the following socio-demographic information and additional information will be collected: age; gender; nationality; marital status; living conditions; education; work status; computer usage; and Internet usage.

### Mediator variables

#### Emotion regulation

A self-developed questionnaire measures the use of the following emotion regulation strategies: distraction; reappraisal; acceptance; rumination/worry; and suppression. Adaptive strategies (distraction, reappraisal, acceptance) are consistently more strongly related with reduced negative affect and maladaptive strategies (rumination/worry and suppression) with enhanced negative affect in laboratory studies [91] and psychopathology in clinical studies [92]. In addition, participants will be asked whether they used problem-solving and attempted to change the stressful situation or contain its consequences. Although problem-solving responses are not directly aimed at regulating emotions, they can have beneficial effects on emotions by modifying or eliminating stressors [92]. Participants will report on the extent to which they have engaged in each of these emotion-regulation strategies on a 6-point scale ranging from 0 (never) to 6 (always). The questionnaire consists of a total of seven items.

#### Behavioral avoidance

Since both interventions stimulate participants to limit their avoidance behavior, this factor will be included in the mediation analyses. Behavioral avoidance is measured with one item (i.e. “In the past week my anxiety caused me to avoid situations and/or activities”), that participants rate on a 6-point-scale ranging from 0 (never) to 6 (always).

#### Treatment expectancy

Treatment expectancy is measured with one item: “How confident are you that the course will be helpful in reducing your anxiety complaints?” Participants rate this question on a 7-point scale ranging from 1 (not at all) to 7 (very confident). Several studies have shown the impact of client expectancies on treatment effect. Evidence suggests that eliciting hope and positive expectations about the effect of the treatment is a crucial factor in many psychotherapies [93–96].

#### Self-efficacy

Preliminary results suggest that the outcome of psychological interventions may be mediated by patient’s self-efficacy with regard to the treatment (i.e. one’s judgment of the capability to successfully participate in and complete the treatment) [97, 98]. Self-efficacy with regard to therapy is measured with one item: “How confident are you that you will do what is required to successfully follow and complete this course?” Participants rate this question on a 7-point scale ranging from 1 (not at all) to 7 (very confident*).*

#### Session Rating Scale

The Session Rating Scale (SRS) [99] will be used to measure the working alliance between the participants and their mental health counselor. The items assess four aspects of the working alliance: the relational bond (the degree to which one feels heard, understood, and respected); the degree to which desired goals and topics of the individual were discussed; an evaluation of the therapist’s approach or method that was used; and an evaluation of how the individual perceives the session overall. Instead of using a visual analogue scale, an 11-point scale will be used to answer each of the four items, with “0” depicting the most negative response and “10” depicting the most positive response. The SRS was shown to have high test–retest and internal consistency reliability, as well as acceptable validity [100, 101]. The SRS will be completed after every face-to-face session.

### Statistical analysis

All analyses will use intention-to-treat principles and a two-tailed alpha of 0.05 for significance testing. Cluster randomization at the level of mental health counselors (instead of individual patients) results in a lack of independence for the outcomes of patients receiving treatment from the same counselor. If clustering and dependence of outcome are ignored, this could lead to underestimation of standard errors and regression coefficients [102]. Therefore, multilevel regression analysis will be used to examine the treatment effect on the primary and secondary outcome measures. Multilevel analysis allows modeling of the variability of the outcome measures within clusters and analysis of a repeated-measure design with missing data. In this cluster randomized RCT, three levels can be distinguished: (1) repeated measures within patients; (2) treatment allocation; and (3) mental health counselors. To evaluate the intervention effect, a twofold analysis will be conducted. First, using a mixed-model analysis with treatment as a dummy variable and the dependent variable on baseline as covariate it will be examined whether conditions differ across time. In addition, a subsequent mixed-model analysis without the dependent variable at baseline as covariate will analyze at which particular time point conditions differ as indicated by the interaction effect of treatment × time. Missing data will be imputed using a model-based approach. Covariance will be estimated using an unstructured covariance matrix.

To examine moderators of the treatment outcome, longitudinal multi-level regression analysis will be performed. Potential moderators will be entered individually in the model. Interaction effects will be investigated (e.g. time × condition × potential moderator). Bivariate latent difference score models will be used for the mediation analysis. This type of analysis is recommended for repeated measurements and multiple mediators, because they allow for a more dynamic approach to mediation, by assessing changes in multiple variables and their interrelations over time [103–105]. Cost-effectiveness analyses will be conducted in agreement with the CHEERS statement [106] and will be determined by relating the difference in healthcare costs (measured with the TiC-P) to the between-group difference in reliable change on GAD-7 scores (cost-effectiveness analysis) and quality-adjusted life-years (QALYs) gained based on the EQ-5D-5 L using the Dutch tariffs (cost–utility analysis). Productivity losses in paid work will be included in the economic evaluation and measured by assessing work-loss days due to absenteeism and work cutback days (presenteeism) while at work but not feeling well. All cost prices will be indexed for the appropriate reference year (likely to be 2017) but not discounted because the study’s time horizon does not exceed the period of a single year. Stochastic uncertainty in the incremental cost-effectiveness ratios (ICERs) will be handled using non-parametric bootstraps (2500 replications), plotted on the ICER plane and depicted in an ICER acceptability curve. Sensitivity analyses will focus on the friction cost versus human capital method and on main cost-drivers.

